**Fig 2 pone.0313664.g002:**
[figure not shown]
Logical Model (Author’s own creation).

### Ethical approval

The Institutional Review Board (IRB) of PHCC (ref no: BUHOOTH-D-24–00059) has reviewed and granted approval for the study on 05/09/2024. Verbal consent will be obtained from participants who are 18 years of age or older for the telephonic survey. The overall planning and execution of the study will be conducted with integrity, in accordance with established ethical principles.

## Discussion

Continuous quality assurance (QA) initiatives are essential for evaluating clinical practices to ensure care is delivered as intended [11]. Diabetes, a chronic condition characterized by elevated blood glucose levels, requires ongoing management to prevent complications and optimize outcomes. Implementing continuous QA efforts is especially critical in both pre-diabetic and diagnosed diabetic populations to sustain effective strategies and enhance patient care [12]. Adherence to established clinical guidelines plays a central role in delaying disease progression and minimizing complications in individuals with type 2 diabetes mellitus (T2DM) [13].

This study was designed to replicate real-world challenges in T2DM management in primary care settings, with the goal of identifying current practice gaps and evaluating the effectiveness of targeted quality improvement initiatives. Through pre- and post-intervention assessments, the study will analyze whether the implemented action plans result in meaningful improvements in care delivery and documentation, or whether unintended consequences emerge. The design facilitates a continuous feedback loop that supports iterative enhancements over time.

The ICAE-DM CARE Study is novel in targeting primary care—the foundational tier where most diabetes management occurs. This setting is particularly relevant in resource-constrained environments. The multi-level intervention strategy combines clinical audits, health provider training, patient engagement, and the use of electronic medical records (EMRs) to facilitate sustainable improvements. Using a quasi-experimental pre-post design, the study integrates both clinical outcomes and patient satisfaction metrics, reflecting a patient-centered approach aligned with global health improvement priorities.

The initial phase of the study involves comprehensive situational analysis through structured chart reviews and telephone-based patient satisfaction surveys. This baseline data allows for a well-rounded understanding of current practices and patients’ experiences.

The findings from this baseline assessment are used to identify deficiencies in clinical practice. Root cause analysis using tools such as fishbone diagrams, process mapping, and SWOT analysis is then conducted to tailor quality improvement (QI) interventions to the context [14,15]. The action plans are implemented collaboratively by a multidisciplinary team, comprising the clinical effectiveness unit, clinical operations, information systems (CIS), and the designated clinical audit champions at each health center.

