Despite these favorable outcomes, there is a notable deficiency in studies investigating the repercussions of an entire audit cycle, particularly regarding chronic disease care, on clinical outcomes and documentation practices. The success of clinical audits largely depends on effectively implementing recommendations in healthcare settings [9]. However, organizational barriers such as limited collaboration between clinicians and management, unclear lines of authority, and differing perspectives can hinder progress. Overcoming these challenges requires fostering a collaborative environment and establishing clear accountability [10].

This study seeks to address a significant gap in literature by evaluating the impact of a systematic clinical audit process on the management and documentation of diabetes within primary care environments. Employing a framework that encompasses both pre- and post-intervention phases in alignment with the ICAE-DM CARE study protocol, this study will evaluate current practices, introduce targeted improvements, and examine the resulting outcomes. The aim is to determine the efficacy of clinical audits in enhancing diabetes care by analyzing variations in diabetes care process indicators, outcome indicators, and related documentation. The results are expected to provide critical insights into the contribution of systematic audit cycles to ongoing quality improvement initiatives. Since 2012, Qatar’s Primary Health Care Corporation (PHCC) has recognized clinical audits as an essential mechanism for ensuring clinical effectiveness, averaging 20–25 audits each year. However, the precise influence of these audits on the management of chronic diseases remains inadequately investigated. This study aims to evaluate the efficacy of clinical audits in improving diabetes care and documentation in accordance with PHCC standards, thereby offering substantial evidence regarding the importance of systematic review processes in enhancing chronic disease management. The study’s methodology, which includes pre- and post-analysis, interventions, and other components, is designed to be replicable across various primary healthcare settings.

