### Sample selection

A stratified simple random sampling method will be employed to select representative samples for both the cross-sectional and cohort components of the study. For the cross-sectional analysis, a total of 450 patient records will be randomly selected from the medical records department across 31 health centers. This sample size was calculated based on a 5% margin of error, a 95% confidence interval, and an assumed response distribution of 50%, with an additional allowance for potential non-responses. The selection will take place at two different time points: baseline and post-intervention, with 450 cases reviewed at each stage to facilitate a comparative analysis of diabetes-related encounters over the preceding three months.

For the patient satisfaction component, a subset of 60 patients will be randomly selected at each time baseline and post-intervention—from the larger cohort. These patients will be contacted by telephone to complete satisfaction surveys, offering qualitative insights into their perceptions of care. The randomization process will be independently applied at both time points to ensure comparability and minimize selection bias. A sample size of 60 patients per time point is considered sufficient to balance feasibility with the need for meaningful analysis of patient satisfaction trends. This approach ensures the robustness and reliability of findings and supports a comprehensive evaluation of both clinical outcomes and patient perspectives throughout the intervention period.

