### Medical record review

The medical record review will be conducted by experienced clinical auditors trained in assessing adherence to evidence-based diabetes management guidelines. Data will be systematically recorded using a customized Excel spreadsheet developed specifically for this study, containing all predefined audit criteria.

The review will focus on newly diagnosed type 2 diabetes mellitus (T2DM) patients, particularly those with an HbA1c value ≥6%, to assess whether appropriate clinical services and interventions were delivered in line with guideline recommendations.

The collected data will allow a comprehensive evaluation of healthcare provider adherence, identifying gaps in clinical care and informing quality improvement initiatives across PHCC settings. *(see*
Table 1
*for data collection variables).*

**Table 1 pone.0313664.t001:** Clinical Audit Criteria and Variables.

Criterion	Description
Criterion 1	ASCVD risk assessment for all adult patients (≥40 years) at diagnosis
Criterion 2.1	Laboratory Investigations: HbA1c, lipid profile (TC, HDL, LDL, TG), serum creatinine and eGFR, liver function (ALT, AST), urine albumin/creatinine ratio, TSH (if dyslipidemia or female >50 years), urine ketones (if glucose >250 mg/dL), serum potassium (if on ACEi/ARB/diuretics)
Criterion 2.2	Initial general foot examination
Criterion 2.3	Referral to eye specialist for initial retinal assessment
Criterion 3	Documentation of HbA1c target goals
Criterion 4	Appropriate treatment initiated or adjusted based on guidelines
Criterion 5	Patient education on diet and physical activity at initial visit
Criterion 6	Referral to dietitian for Medical Nutrition Therapy (MNT)
Criterion 7	Follow-up HbA1c test ordered within 3–6 months from treatment initiation

Source: PHCC clinical practice guideline for the management of Type 2 Diabetes.

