## Conclusion

This comprehensive study underscores the pivotal role of clinical audits in enhancing the quality of diabetes care within primary healthcare settings. By systematically assessing current practices, identifying care gaps, and implementing targeted multidisciplinary interventions, the ICAE-DM CARE study aims to demonstrate measurable improvements in clinical management, documentation, and patient satisfaction among adults with T2DM. The pre- and post-intervention design provides robust evidence on the effectiveness of structured quality improvement initiatives, highlighting their potential to foster sustainable changes and elevate standards of care. Findings from this study will offer valuable insights into the integration of audit cycles into routine practice, emphasizing the importance of collaborative efforts, continuous monitoring, and data-driven strategies. Ultimately, this approach can serve as a scalable model for primary care facilities worldwide seeking to optimize chronic disease management and improve patient outcomes through systematic quality assurance processes.

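### Outcome indicators and clinical outcomes are promised, but all nine Table 1 criteria are process or documentation items, four of them visible mainly through the clinician's entry

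*Protocol article*

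**What the plan says.** Three places in the protocol article promise outcomes. The aim in the Introduction is to be met by "analyzing variations in diabetes care process indicators, outcome indicators, and related documentation", after the same section has named missing evidence on clinical outcomes as part of the literature gap. Sample selection says that the approach "supports a comprehensive evaluation of both clinical outcomes and patient perspectives throughout the intervention period". The Discussion says that "the study integrates both clinical outcomes and patient satisfaction metrics".

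Medical record review describes what is collected. The spreadsheet is described as "containing all predefined audit criteria", and the reader is sent to Table 1 for the variables. The purpose of the review is "to assess whether appropriate clinical services and interventions were delivered in line with guideline recommendations". Two Table 1 rows that mention HbA1c read "Documentation of HbA1c target goals" and "Follow-up HbA1c test ordered within 3–6 months from treatment initiation".

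Evaluation of audit impact, within the Discussion, names two domains, care delivery and documentation. As its key outcome indicators it gives risk assessment documentation, referrals, completed laboratory tests and patient education.

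**The concern.** The stated aim and the variable list do not match. An analysis plan can settle how a variable is analysed, but it cannot analyse a patient result that the collection sheet does not hold. If the label stays, a rise in tests ordered or goals recorded could be reported as an improvement in clinical outcomes. Evaluation of audit impact would then use meaningful improvements as the basis for scaling the strategy to other settings.

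A narrower second issue concerns what some criteria measure. The role of clinical audit champions lists documentation practices among the changes made, with HbA1c goal setting and foot examination as examples. Those are Criteria 3 and 2.2. Where an item is visible mainly as a chart entry and the intervention works on charting, a higher score need not mean that patients received more care.

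**Working it through.** The main check is one of content: each Table 1 row is classified by what it records.

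- Criterion 1: ASCVD risk assessed. Process, seen mainly through the clinician's entry.
- Criterion 2.1: laboratory panel. Process, with an order and a result in the system.
- Criterion 2.2: foot examination. Process, seen mainly through the entry.
- Criterion 2.3: eye referral. Process, with a referral trace.
- Criterion 3: HbA1c goal recorded. Purely documentation.
- Criterion 4: treatment in line with the guideline. Process, with a treatment trace.
- Criterion 5: diet and activity education. Process, seen mainly through the entry.
- Criterion 6: dietitian referral. Process, with a referral trace.
- Criterion 7: repeat HbA1c ordered. Process, with an order trace.

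Result: patient results, 0 of 9. Mainly dependent on an entry, 4 of 9 (1, 2.2, 3, 5). With their own trace, 5 of 9 (2.1, 2.3, 4, 6, 7). The split between four and five is a judgement on how such items are normally stored; the article has no rule that assigns criteria to its two domains.

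**The plan's own figure.** The 450 records per time point are sized for the precision of one proportion: n = 1.96² × 0.25 / 0.05² = 384.1, so 385. The non-response allowance is not given; 450 implies 1 − 385/450 = 14.4%, or 450/385 − 1 = 16.9%, depending on how it was applied. The figure is plausible for yes/no criteria. It was not derived for a clinical outcome.

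**The survey as a check on charting.** Questions 1 to 5 ask patients what the doctor did, so they are a source outside the chart. With 60 per time point, the 95% half-width for a pre-post difference near 50% is 1.96 × √(0.5/60) = 17.9 percentage points. For 450 records it is 1.96 × √(0.5/450) = 6.5 points. The survey could therefore confirm only large changes, and the article describes no comparison with the chart.

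**If HbA1c were added.** The article gives no standard deviation, so 1.5 to 2.0 percentage points is assumed. With two-sided alpha 0.05 and 80% power, the detectable mean difference is (1.96 + 0.84) × SD × √(2/450), that is 0.28 (SD 1.5) to 0.37 (SD 2.0). This takes a value for all 450 records per wave and ignores clustering in 31 centers. Fewer retested patients, or clustering, would make it larger.

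**The case against.** The strongest reply is that the article shows what it means. Evaluation of audit impact spells out its outcome indicators, the Abstract lists documentation, co-morbidity assessment, screening, adherence and satisfaction, and Table 1 fits those aims. On that reading the fault is loose wording. This stands in part: the design does suit a process audit, and rewording is a sufficient remedy. It does not remove the point, because clinical outcomes are promised separately in three sections and the relabelling is what would carry the overclaim into the results.

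A second reply is that this is a condensed article. Figure 2 is not shown, Data collection procedures speaks generally of pertinent variables, HbA1c values must be read to focus the review, and a t test is mentioned. An outcome defined elsewhere cannot be excluded. But none is named, and the article presents Table 1 as the variable list.

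A reader might infer more than the document supports:

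- That the study cannot separate better care from better charting at all. Five criteria normally leave an order, result, referral or treatment trace, the survey gives some information from outside the chart, and documentation is itself a declared target.
- That the Conclusion promises clinical outcomes too. It says the study "aims to demonstrate measurable improvements in clinical management, documentation, and patient satisfaction among adults with T2DM", which is within what is measured, apart from the charting caveat.
- That 60 patient-record pairs per wave are available for an agreement check at no cost. Sample selection draws the 60 from the larger cohort without saying that their records are audited, and Ethical approval describes consent for the telephone survey without mentioning linkage.

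**Conclusion.** The point holds in limited form and should be corrected. With 0 of 9 criteria a patient result, the plan as written can support no conclusion on clinical outcomes, although the Introduction, Sample selection and the Discussion promise one. For 4 of the 9 criteria, a rise between waves cannot by itself be read as better care; for the other 5 that objection is much weaker. This rests on three assumptions: Table 1 is the full list of review variables, as Medical record review presents it; no outcome is defined only in the figures that are not shown; and orders, results, referrals and treatment are stored in the electronic record separately from the clinician's note. The main comparison of process and documentation between waves is not invalidated.

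**What to change.** Choose one of two routes.

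(a) Replace outcome indicators and clinical outcomes in the Introduction, Sample selection and the Discussion with process and documentation indicators, correct the label in Evaluation of audit impact, and limit the conclusion accordingly. The cost is a change of wording.

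(b) Add three columns to the sheet: the HbA1c value at diagnosis, the first follow-up HbA1c value, and its date. Report them by wave beside the proportion retested, as a supportive outcome. Retesting is itself an audit target, so the intervention may change who has a follow-up value, and adjusting for the value at diagnosis does not remove that selection. The three-month look-back in Sample selection must also be reconciled with the 3–6 month window in Criterion 7, since many follow-up values would otherwise fall outside the period reviewed. The records are already being opened, but the change of window makes this more than three extra columns.

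Under either route, report Criteria 1, 2.2, 3 and 5 as documentation-dependent, separately from those with an order, result, referral or treatment trace. This needs no new data. Linking survey answers to records is optional, and only if the 60 patients are drawn from the audited records and consent covers it.

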### The role of clinical audit champions

Clinical audit champions play a key role in bridging the gap between strategic planning and on-the-ground implementation. They are responsible for coordinating local efforts, monitoring compliance with action plans, and reporting progress [16–18]. In this study, clinical audit champions were instrumental in tracking implementation activities at the health center level. They maintained logs and shared periodic updates during six-weekly regional meetings organized by the clinical effectiveness team. These meetings served to track key metrics, troubleshoot challenges, and document improvements or barriers encountered during implementation.

Importantly, audit champions were authorized, in coordination with health center managers, to implement changes aligned with the approved QI plan. Changes implemented included improvements in documentation practices (e.g., timely HbA1c goal setting, foot exam documentation), adherence to referral protocols, and patient counseling activities. These modifications were monitored using structured tracking forms and validated during follow-up audits, providing clear evidence of implementation progress.

### Structured follow-up and monitoring

A formal follow-up structure was embedded into the protocol, where clinical audit champions and regional clinical effectiveness focal points conducted collaborative reviews every six weeks. These recurring sessions allowed champions to present updates, share challenges, and receive guidance. This structured follow-up ensured accountability and supported the continuity and sustainability of changes implemented during the intervention phase.

### Evaluation of audit impact

The effectiveness of the clinical audit was assessed across two domains: clinical care delivery and documentation practices. Improvements in risk assessment documentation, appropriate referrals, lab test completion, and patient education were key outcome indicators. In centers where outcomes were not achieved, qualitative insights revealed constraints such as staff turnover, limited training continuity, and EMR documentation challenges as contributing factors.

The post-intervention phase, scheduled 8–9 months after implementation, mirrors the baseline assessment in design and sample size. The use of consistent tools—open chart reviews and structured surveys ensures comparability between the two data points.

Final comparative analysis will assess the extent of change in care quality indicators and documentation standards following the audit. Where meaningful improvements are found, the results will serve as a basis for scaling similar QI strategies in other primary care settings. Where improvements are minimal, the study will inform refinements in implementation strategies, emphasizing adaptability in quality improvement processes.

This protocol offers a replicable, resource-sensitive model of continuous quality improvement in chronic disease care. Its structured, scalable methodology—rooted in evidence, stakeholder involvement, and iterative evaluation—contributes meaningfully to advancing primary care practices globally.

## Conclusion

This comprehensive study underscores the pivotal role of clinical audits in enhancing the quality of diabetes care within primary healthcare settings. By systematically assessing current practices, identifying care gaps, and implementing targeted multidisciplinary interventions, the ICAE-DM CARE study aims to demonstrate measurable improvements in clinical management, documentation, and patient satisfaction among adults with T2DM. The pre- and post-intervention design provides robust evidence on the effectiveness of structured quality improvement initiatives, highlighting their potential to foster sustainable changes and elevate standards of care. Findings from this study will offer valuable insights into the integration of audit cycles into routine practice, emphasizing the importance of collaborative efforts, continuous monitoring, and data-driven strategies. Ultimately, this approach can serve as a scalable model for primary care facilities worldwide seeking to optimize chronic disease management and improve patient outcomes through systematic quality assurance processes.

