### Study settings

All 31 PHCC health centers providing diabetes care will be included. Data will be collected from stored electronic medical records and direct input from service users. The review of clinical guidelines will be conducted via online access to the PHCC intranet. Additionally, medical records will be reviewed through the Clinical Information System (CIS), and patient satisfaction will be assessed through structured telephone interviews.

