### Intervention and follow-up

Following the initial cross-sectional analysis, identified gaps in care quality and patient satisfaction will inform the development of a comprehensive action plan. This plan will be implemented across all participating health centers to address the deficiencies and enhance service delivery. The intervention will be embedded into standard auditing procedures to ensure continuous quality improvement.

The intervention phase will last approximately 8–9 months. Afterward, a second round of data collection will be conducted using the same methodology and variables to ensure consistency and enable direct comparison. This approach will support the evaluation of changes in clinical performance and patient experience before and after the intervention *(see*
Fig 1
*for the study flow chart).*

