### Analytical plan

Data will be extracted from the electronic health record system at two separate points: one time at a point before the intervention and the other time at a point after the implementation of the intervention. Excel will be used to collect and organize the data. PivotTables will be used to determine the frequency of cases across variables. Excel will be further used to produce histograms and other figures.

Study outcome variables will be assessed using independent tests like Chi square or t test to compare between the two groups. For satisfaction, we will do it frequently by percentage P=(F/T) *100.

The statistical analysis will be performed using STATA 15.1 (College Station, TX, USA). A Wilcoxon sign rank test will be used to find the mean difference between the pre- and post-assessment. P < 0.05 will be considered statistically significant. A logical model of protocol presented in Fig 2.

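### With every centre exposed and only two snapshots, the comparison cannot separate the intervention from background trend, so the claim of robust evidence of effectiveness is not supported

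*Protocol article*

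**What the plan says.** Study settings: "All 31 PHCC health centers providing diabetes care will be included". Intervention and follow-up: "This plan will be implemented across all participating health centers to address the deficiencies and enhance service delivery". No unexposed centre, staggered start or external comparison is described.

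Analytical plan: "Data will be extracted from the electronic health record system at two separate points", specified as "one time at a point before the intervention and the other time at a point after the implementation of the intervention". The two groups of records are compared by chi-square or t test at P < 0.05, with no adjustment for time. Sample selection sets 450 records at each stage, covering encounters in the preceding three months.

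The Conclusion then states: "The pre- and post-intervention design provides robust evidence on the effectiveness of structured quality improvement initiatives". The Abstract makes a similar claim of robust evidence for building audits into routine diabetes care. Evaluation of audit impact makes observed improvement the basis for scaling the strategy up. The article names no limitation of the uncontrolled design.

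On background activity, the Introduction reports that the provider has run clinical audits since 2012, "averaging 20–25 audits each year".

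**The concern.** A before-after difference estimates an intervention effect only if nothing else would have moved the indicator between the two dates. The plan contains nothing that could show this. The comparability that the article attributes to using the same tools in both rounds covers measurement, not what would have happened without the intervention. Aiming the action plan at gaps found at baseline also invites regression to the mean.

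The stake is the main conclusion. A drift that would have occurred anyway could be reported as the effect of the audit cycle and lead to scale-up elsewhere. More records do not help: the bias stays the same size as the sample grows, and the test becomes more likely to declare it significant.

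**Working it through.** **Step 1. The plan's own figure.** Inputs from Sample selection: margin 5%, 95% confidence, proportion 50%. n = 1.96² × 0.5 × 0.5 / 0.05² = 384.1, so 385. The allowance for non-response is not quantified. 450 implies 1 − 385/450 = 14.4%, or 450/385 − 1 = 16.9%, depending on how it was applied. So 450 is reproduced as a precision figure for a single proportion. Used for the comparison, 450 v 450 detects a difference of about 9.3 points from 50% with 80% power.

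**Step 2. What two points can identify.** Let a be the starting level, b the background trend per month, T the months between snapshots and d the intervention effect. The expected values are a before and a + bT + d after, so their difference is bT + d. There are two observed means and three unknowns (the design matrix has rank 2), so d cannot be separated from bT.

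**Step 3. Rejection with no intervention effect.** Set d = 0 and let the proportion drift from p1 to p2. Use the pooled two-proportion test, two-sided 0.05 (the article does not state sidedness), n = 450 per wave, records independent.

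P(reject) ≈ Φ((δ − 1.96·SE0)/SE1) plus the opposite tail, where δ = p2 − p1, SE0 = √(2·p̄(1 − p̄)/n), p̄ is the mean of p1 and p2, and SE1 = √([p1(1 − p1) + p2(1 − p2)]/n).

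For 50% to 55%: SE0 = √(2 × 0.525 × 0.475/450) = 0.0333, SE1 = 0.0332, and Φ(−0.459) = 0.32. The opposite tail is negligible.

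| Assumed drift | From 50% | From 70% |
|---|---|---|
| 0 points | 0.05 | 0.05 |
| 2 points | 0.09 | 0.10 |
| 3 points | 0.15 | 0.17 |
| 5 points | 0.32 | 0.39 |
| 10 points | 0.86 | 0.94 |

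**Step 4. Spacing of the windows.** Intervention and follow-up puts the second round after a phase of 8–9 months. Evaluation of audit impact puts it 8–9 months after implementation. The time for baseline analysis and action planning is not given. The window midpoints could therefore be about 8–9 months apart (different season), about 11–12 (nearly the same season) or 16 or more. Under an assumed drift of 0.5 points a month from 50%, gaps of 8.5, 11.5 and 15 months give drifts of 4.25, 5.75 and 7.5 points and rejection in about 25%, 41% and 62% of studies. The trend problem holds under every reading; the season problem depends on dates that are not fixed.

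**Step 5. What a monthly series would add.** Segmented regression with level, trend, level change and slope change, leaving out a 9-month implementation phase, at p = 0.5. Detectable level change (80% power) = 2.80 × its standard error. Monthly volumes and autocorrelation are assumptions.

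| Pre + post months | Records/month | No autocorrelation | Autocorrelation 0.3 |
|---|---|---|---|
| 24 + 12 | 450 | 5.7 points | 7.3 points |
| 24 + 12 | 200 | 8.5 points | 10.9 points |
| 12 + 3 | 450 | 10.6 points | 12.6 points |
| 12 + 3 | 200 | 16.0 points | 18.8 points |
| 24 + 12 | 25 (the planned 900 spread out) | 24 points | 31 points |

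A short series is less sensitive than the two-wave comparison (10.6 against 9.3 points). Twelve pre-intervention months contain each calendar month once, so they cannot separate season from trend. Spreading the 900 manual reviews over the months would not work either. A useful series needs bulk extraction and a long run.

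**The case against.** **The design is labelled quasi-experimental, and the final analysis is described as assessing the extent of change.** True, and that wording is sound. But the label supplies no counterfactual, and the Abstract and Conclusion go further than change.

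**No background drift is documented.** This stands in part. A reader might infer from the provider's audit activity that improvement would probably have occurred anyway. The Introduction does not say that those audits concern diabetes, and says that their influence on chronic disease care has been too little studied. Background change is plausible; the document does not show it to be likely. The drift sizes are assumptions, and at 2 or 3 points the false-positive rate is modest (9% or 15%).

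**Season may not differ.** This stands. A reader might take the 8–9 month phase to mean that the windows must fall in different months. With about three months of planning they would nearly coincide.

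**Does baseline come after some of the changes?** The section on audit champions reports in the past tense: "Changes implemented included improvements in documentation practices". The two sections after it also speak of completed follow-up and assessment, in a study dated July 2025 to July 2027. A reader might infer that change began before baseline. The document does not support that: Intervention and follow-up places the action plan after the baseline analysis and derives it from the gaps found there. The tense clash needs reconciling but does not show a contaminated baseline.

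**A monthly series would not cure the problem.** Largely accepted. The structured items (laboratory tests, eye and dietitian referrals, follow-up HbA1c order) correspond to 4 of the 9 rows of Table 1. The rest, and the telephone survey, would stay two-point. A simultaneous change in the record system or another initiative would also produce a break.

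**Conclusion.** The point holds. Calendar time and intervention are completely confounded by the stated design, so the planned comparison can show that indicators changed but not that the audit cycle changed them. The claim of robust evidence of effectiveness should be withdrawn from the Conclusion and its counterpart in the Abstract, and the scale-up conclusion should carry the limitation.

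The confounding itself needs no numerical assumption. Its size does: the range of about 9% to 86% assumes a drift of 2 to 10 points from 50%, a two-sided 0.05 test, and 450 independent records per wave with clustering by centre ignored. The document gives no drift, baseline rates or monthly volumes, so these figures illustrate the risk and do not predict it.

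**What to change.** 1. **Restate the claim.** In the Abstract and Conclusion, describe the result as before-after change. Name the uncontrolled design as a limitation of any effectiveness or scale-up conclusion. Cost: wording only.

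2. **Fix the dates.** Give the dates of the two three-month windows, in the same calendar months, with baseline before the first implemented change, and state the date of that change. Reconcile the past-tense text in the sections on audit champions, structured follow-up and evaluation of audit impact with the July 2025 to July 2027 period. Cost: possibly moving the second audit within the two-year period.

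3. **Add a supportive series.** For items confirmed to be structured fields (laboratory tests, eye and dietitian referrals, follow-up HbA1c order), extract monthly counts for all eligible patients and fit a segmented regression beside the 450-record audit. Use preferably at least 24 pre-intervention months and as many post-intervention months as the study period allows. Check monthly volumes first. Cost: one further extraction and analysis, with no extra patients. The work includes applying the refill-only exclusion and the conditional laboratory denominators of Criterion 2.1.

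What remains: the other five Table 1 rows and the telephone survey stay two-point. A break in the series would strengthen the case but would not by itself restore an effectiveness claim, because a concurrent change in the record system or a co-intervention would not be excluded.
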